## Abstract

**Background:**

The World Health Organization recommends all men who have sex with men (MSM) receive Hepatitis B Virus (HBV) and Hepatitis C Virus (HCV) testing. MSM in China are a high-risk group for HBV and HCV infection, but test uptake is low. Crowdsourcing invites a large group to solve a problem and then shares the solution with the public. This nationwide online randomized controlled trial will evaluate the effectiveness of a crowdsourced intervention to increase HBV and HCV testing among MSM in China.

**Methods:**

Seven hundred MSM will be recruited through social media operated by MSM organizations in China. Eligible participants will be born biologically male, age 16 years or older, report previous anal sex with another man, and reside in China. After completing a baseline online survey, participants will be randomly assigned to intervention or control arms with a 1:1 allocation ratio. The intervention will include two components: (1) a multimedia component will deliver two videos and two images promoting HBV and HCV testing developed through a crowdsourcing contest in China; (2) a participatory component will invite men to submit suggestions for how to improve crowdsourced videos and images. The control arm will not view any images or videos and will not be invited to submit suggestions. All participants will be offered reimbursement for HBV and HCV testing costs. The primary outcome is HBV and HCV test uptake confirmed through electronic submission of test report photos within four weeks of enrolment. Secondary outcomes include self-reported HBV and HCV test uptake, HBV vaccination uptake, and change in stigma toward people living with HBV after four weeks. Primary and secondary outcomes will be calculated using intention to treat and as-exposed analyses and compared using two-sided 95% confidence intervals.

**Discussion:**

Few previous studies have evaluated interventions to increase HBV and HCV testing in middle-income countries with a high burden of hepatitis. Delivering a crowdsourced intervention using social media is a novel approach to increasing hepatitis testing rates. HBV and HCV test uptake will be confirmed through test report photos, avoiding the limitations of self-reported testing outcomes.

**Trial registration:**

NCT03482388 (29 March 2018).

**Electronic supplementary material:**

The online version of this article (10.1186/s12879-018-3403-3) contains supplementary material, which is available to authorized users.

## Background

Hepatitis B Virus (HBV) and Hepatitis C Virus (HCV) are substantial contributors to global morbidity and mortality, together accounting for more deaths annually than HIV [1]. Most individuals affected by chronic viral hepatitis are in low- and middle-income countries (LMIC) [2]. China is a middle-income country with a high burden of hepatitis [3]. HBV and HCV prevalence among the general population in China is 7% and 0.8%, respectively, and China alone has more persons living with chronic viral hepatitis than Europe and the Americas combined [2–4].

Men who have sex with men (MSM) are a group at increased risk for HBV and HCV infection [5, 6]. Prevalence of HBV and HCV is higher among MSM than the general population in multiple contexts, [7–10] including China [11, 12]. As a result, the World Health Organization (WHO) guidelines recommend all MSM receive HBV and HCV testing at least once [13]. Testing is the key first step in the viral hepatitis care continuum and is necessary for infected persons to be linked to care, initiated on treatment, and to achieve viral suppression or cure. Expedited linkage to the viral hepatitis care continuum can reduce liver-related deaths, [14, 15] and hepatitis testing can identify those susceptible to HBV infection and facilitate vaccination [16].

Despite the importance of testing, HBV and HCV testing rates among MSM in China are low. A 2017 nationwide online survey of MSM in China found 59% had never HCV tested, and among those with no or uncertain HBV vaccination, 62% had never HBV tested [17]. Chinese MSM who had not HBV or HCV tested were also less likely to have received screening for HIV and other sexually transmitted infections (STI) [17]. Novel methods of increasing hepatitis testing and linkage to HIV/STI testing services among MSM are needed.

HBV and HCV testing services can be potentially strengthened using crowdsourcing. Crowdsourcing invites a large group to solve a problem and then shares the solution with the public [18]. This bottom-up approach can spur innovation through collecting and refining a wide-range of creative solutions from a diverse group of contributors [13]. Additionally, crowdsourcing engages communities in the development of responses to important issues, thereby increasing community participation and producing more locally relevant solutions [19, 20].

Crowdsourcing has been used to identify health innovation by many funders, including the United States National Institutes of Health, the English National Health Service, the Bill and Melinda Gates Foundation, and the United States government [21, 22]. Non-inferiority randomized controlled trials (RCTs) have shown that crowdsourcing is a cost-effective tool for increasing HIV testing uptake and is as efficacious as evidence-based health marketing materials [23, 24]. Additionally, social media interventions that involve active participation and content generation, such as crowdsourcing, have been associated with higher rates of HIV and STI testing compared to passive testing campaigns [25].

Few previous studies have evaluated interventions to increase hepatitis testing in LMIC, and none of these have targeted MSM or used a crowdsourcing approach [26]. The purpose of this RCT is to address this gap in the current literature and evaluate the impact of a crowdsourced intervention on HBV and HCV test uptake among MSM in China.

### Objectives

Specific aim 1: To compare confirmed HBV and HCV test uptake as a composite endpoint between MSM randomly assigned to a crowdsourced intervention and MSM randomly assigned to control.

Hypothesis 1: MSM assigned to the crowdsourced intervention will have a higher rate of HBV and HCV test uptake compared to MSM in the control arm.

Specific aim 2: To compare change in stigma toward people living with HBV between MSM randomly assigned to a crowdsourced intervention and MSM randomly assigned to control.

Hypothesis 2: MSM assigned to the crowdsourced intervention will have greater reduction in stigma toward people living with HBV compared to MSM in the control arm.

Specific aim 3: To compare self-reported linkage to clinical visits about hepatitis, HBV vaccination, and HIV/STI testing services between MSM randomly assigned to a crowdsourced intervention and MSM randomly assigned to control.

Hypothesis 3: MSM assigned to the crowdsourced intervention will have improved linkage to clinical visits about hepatitis, HBV vaccination, and HIV/STI testing services compared to MSM in the control arm.

## Methods

### Trial design and timeline

This study will be an online superiority RCT. After completing a baseline survey to assess eligibility, enrolled participants will be randomly assigned in a 1:1 ratio into the intervention or control arms. Men randomly assigned to the intervention arm will be asked to view four crowdsourced images and videos promoting hepatitis testing over 8 days. After viewing each image or video men will be invited to submit suggestions for how to better tailor the crowdsourced materials to the MSM community. Men randomly assigned to the control arm will view no materials and will not be invited to submit suggestions. Participants can submit photos of hepatitis test reports to confirm HBV and HCV test uptake at any time after enrolment. After 3 weeks men will be sent a message asking them to complete a follow-up survey within 1 week. All participants will be assessed for primary and secondary outcomes at 4 weeks (28 days) post-enrolment (Table 1). The study is anticipated to begin enrolment in April 2018 and finish data collection by June 2018. A flowchart summarizing trial design and timeline is presented in Fig. 1.

**Table 1 Tab1:** Primary and secondary outcomes with definitions

Primary outcome	Definition
Confirmed HBV and HCV test uptake	Defined as men who had both HBsAg test uptake and anti-HCV IgG test uptake confirmed through electronic submission of a test report photo showing serology results, age of tester, sex of tester, and date of test within four weeks of enrolment
Secondary outcomes	
Confirmed HBV test uptake	Defined as men who had HBsAg test uptake confirmed through electronic submission of a test report photo showing serology results, age of tester, sex of tester, and date of test within four weeks of enrolment
Confirmed HCV test uptake	Defined as men who had anti-HCV IgG test uptake confirmed through electronic submission of a test report photo showing serology results, age of tester, sex of tester, and date of test within four weeks of enrolment
Self-reported HBV test uptake	Defined as men who had HBsAg uptake within four weeks of enrolment, self-reported in follow-up survey
Self-reported HCV test uptake	Defined as men who had anti-HCV IgG uptake within four weeks of enrolment, self-reported in follow-up survey
HBV vaccination uptake	Defined as men who had receipt of at least a one dose of the HBV vaccine within four weeks of enrolment, self-reported in follow-up survey
HBV vaccination uptake among men with confirmed susceptibility to HBV infection	Defined as men with negative HBsAg and negative anti-HBs results confirmed through electronic submission of a test report photo showing serology results, who had receipt of at least one dose of the HBV vaccine within four weeks of enrolment, self-reported in follow-up survey
HIV test uptake	Defined as men who had HIV test uptake within four weeks of enrolment, self-reported in follow-up survey
Chlamydia test uptake	Defined as men who had chlamydia test uptake within four weeks of enrolment, self-reported in follow-up survey
Gonorrhoea test uptake	Defined as men who had gonorrhoea test uptake within four weeks of enrolment, self-reported in follow-up survey
Syphilis test uptake	Defined as men who had syphilis test uptake within four weeks of enrolment, self-reported in follow-up survey
Change in stigma toward people living with HBV	Continuous variable, defined as difference between Toronto Chinese HBV Stigma Scale score assessed at follow-up and baseline. Stigma toward people living with HBV will be measured at baseline and follow-up using 20 survey items that are each on a five point Likert scale. The 20 items were originally developed as the Toronto Chinese HBV Stigma Scale (potential range of 20–100), which has been previously validated and correlated to HBV testing behaviours among Chinese populations [39]. Decreased stigma toward people living with HBV will be defined as a mean composite score that is less at follow-up compared to baseline.
Visit with a physician after hepatitis test uptake	Defined as men who had HBV and/or HCV test uptake and saw a physician to discuss hepatitis test results within four weeks of enrolment, self-reported in follow-up survey

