### Eligibility criteria

Potential participants must first agree to an online informed consent before beginning the baseline online survey. Inclusion criteria are being born biologically male, age 16 years or older, self-reported previous anal sex with another man, and current residence in China. Men who report past HBV vaccination, HBV testing, or HCV testing will be excluded. Those who report uncertain past HBV vaccination, HBV testing, or HCV testing will be considered eligible. All eligible participants must provide a working unique mobile phone number and WeChat account to be enrolled.

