### Data collection and measures

Baseline and follow-up surveys will be delivered to mobile devices and completed online using Wenjuanxing (Sojump, Shanghai, China), a web-based survey tool that meets industry standards for security and functionality. Both surveys were written in Chinese, and 12 local MSM were asked to provide feedback to ensure questions are clear and culturally appropriate.

The baseline survey will first ask respondents to answer questions regarding eligibility criteria. If eligible, respondents will be asked to complete the remainder of the survey. The baseline survey will include the following domains: sociodemographic characteristics, sexual risk factors for viral hepatitis infection, previous HIV/STI testing behaviours and diagnoses, stigma toward people living with HBV, engagement in health promotion activities in the MSM community, access to primary healthcare services, access to MSM-competent healthcare, experiences with MSM stigma in healthcare settings, and trust in healthcare providers. Twenty-eight questions will measure sexual risk factors for viral hepatitis infection, which were adapted from the validated HCV-MOSAIC risk score for HCV infection among MSM [30]. Stigma toward people living with HBV will be assessed using the Toronto Chinese HBV Stigma Scale, a 20-item index validated for Chinese-speaking populations [12]. Engagement in health promotion activities will be measured through six items used in previous evaluations of crowdsourced interventions [31]. Access to MSM-competent healthcare will be assessed through three questions adapted from a recent survey investigating MSM-competent physicians in China [32]. Seven questions adapted from research in the United States will be used to measure experiences with MSM stigma in healthcare settings and trust in healthcare providers [33, 34].

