#### Secondary analyses

The intervention and control arms will also be compared for differences in proportions of men achieving secondary outcomes, including confirmed HBsAg test uptake (independent of anti-HCV IgG test uptake), confirmed anti-HCV IgG test uptake (independent of HBsAg test uptake), self-reported HBsAg and anti-HCV IgG test uptake, HBV vaccination, and HIV and STI test uptake during the four-week study period. The analysis approach will be as described for the primary outcome. Change in stigma toward people living with HBV from baseline to week four will be calculated and compared between the intervention and control arms using a Wilcoxon ranksum test.

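### HIV test uptake is defined in all randomised men, including those with a known HIV diagnosis, which dilutes the risk difference without biasing the comparison (minor)

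*Protocol article*

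**What the plan says.** - **Eligibility (Eligibility criteria).** "Inclusion criteria are being born biologically male, age 16 years or older, self-reported previous anal sex with another man, and current residence in China". The history-based exclusion concerns hepatitis only: "Men who report past HBV vaccination, HBV testing, or HCV testing will be excluded". HIV status appears in neither list.
- **Outcome (Table 1).** HIV test uptake is "Defined as men who had HIV test uptake within four weeks of enrolment, self-reported in follow-up survey".
- **Hypothesis served (Objectives).** Hypothesis 3 expects "improved linkage to clinical visits about hepatitis, HBV vaccination, and HIV/STI testing services compared to MSM in the control arm".
- **Analysis (Secondary analyses, Missing data plan).** "The analysis approach will be as described for the primary outcome", meaning a difference in proportions by randomised arm. Men lost to follow-up stay in the denominator as not having achieved the outcome.
- **Baseline data (Data collection and measures).** The baseline survey, completed before randomisation, covers "previous HIV/STI testing behaviours and diagnoses".
- **A restricted outcome in the same table.** HBV vaccination uptake appears twice, once for all men and once for a susceptible group: "Defined as men with negative HBsAg and negative anti-HBs results confirmed through electronic submission of a test report photo". HIV test uptake has only the all-men version.

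**The concern.** A man who already knows he has HIV cannot be newly linked to HIV testing. In this outcome he can appear in two ways. He reports no test and is a non-event whatever the intervention does, or he reports a monitoring blood test as an HIV test and is an event that is not linkage to testing. Neither carries information about Hypothesis 3.

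HIV is the one listed infection test for which this argument is clear. Chlamydia, gonorrhoea and syphilis can be acquired again, so a repeat test after a past diagnosis still has meaning.

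What is at stake is the size and the meaning of the estimate for one self-reported secondary outcome. The effect on men who could take up an HIV test would be understated on the absolute scale, and the reported proportions would describe a mixture of men at risk and men already diagnosed.

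**Working it through.** **The plan's own figure.** The only sample size statement concerns the primary outcome: 8.5% vs 3.0%, two-sided 5%, exact test, 10% not evaluable. Full enumeration of Fisher's exact test gives 303 per arm as the smallest size with 80% power (0.8003). Then 606 / 0.90 = 673.3, rounded up to 674, as stated. With 700 enrolled, 315 per arm are evaluable and power is 0.818, which agrees with the stated 82%. Nothing below touches these figures.

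**Inputs for HIV test uptake.** The documents give neither an HIV testing rate nor the share *f* of men with a known diagnosis. Assumptions: *f* from 2% to 15%; uptake in men at risk of 40% vs 30%; 350 per arm.

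**Formulas.** Let *p*I and *p*C be uptake in men at risk, and *m* the proportion of known-positive men who report a test, equal in both arms.

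- Observed proportion in an arm: *p*(1 − *f*) + *m f*
- Observed difference: (1 − *f*)(*p*I − *p*C), because the *m f* term cancels
- If *m* = 0 the risk ratio is unchanged. If *m* > 0 it moves towards 1.

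**Worked case, *f* = 10%.**

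- *m* = 0: 0.40 × 0.90 = 36% vs 0.30 × 0.90 = 27%. The difference is 9.0 points and the ratio 36/27 = 1.33, as in men at risk (40/30 = 1.33).
- *m* = 0.5: 36% + 5% = 41% vs 27% + 5% = 32%. The difference is still 9.0 points, but the ratio falls to 41/32 = 1.28.
- Restricted to men at risk: 350 × 0.90 = 315 per arm, 40% vs 30%, difference 10.0 points.

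**Range (unpooled z-test, two-sided 5%).**

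| *f* | Difference, all men (points) | Power, all men, *m* = 0 | Power, all men, *m* = 0.5 | Power, restricted to men at risk |
|---|---|---|---|---|
| 2% | 9.8 | 0.784 | 0.778 | 0.788 |
| 5% | 9.5 | 0.765 | 0.750 | 0.776 |
| 10% | 9.0 | 0.731 | 0.700 | 0.754 |
| 15% | 8.5 | 0.695 | 0.646 | 0.729 |

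With *m* = 0, restriction gains 0.4 points of power at 2% (0.788 − 0.784) and 3.4 points at 15% (0.729 − 0.695). With 30% vs 20% in men at risk the differences are the same, since only the 10-point gap enters, and the gain at 15% is about 2 points. Restriction loses men but no power, because the men removed add no signal.

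**The case against.** **The population is the one the hypothesis names.** Hypothesis 3 compares MSM by assigned arm and does not exclude men with HIV. An all-randomised denominator matches it and suits a pragmatic trial. This stands in part: the plan does not contradict itself, and a reader who infers that the hypothesis is tested in the wrong population goes too far. The all-men analysis answers a legitimate but less useful question.

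**There is no between-arm bias.** HIV status at baseline precedes randomisation. This stands fully. A reader might infer that the comparison is invalid, and it is not.

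**The share may be small.** The assumed range has no source in the documents. The Background reports that MSM untested for hepatitis were also less likely to have been screened for HIV, and the trial excludes men who report a past hepatitis test. That points to fewer known diagnoses. This stands. At 2% the effect is negligible.

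**Monitoring tests reported as HIV tests.** It is tempting to claim a substantial number of false events. That depends on the wording and routing of the follow-up survey, an additional file that is not shown. The *m* = 0.5 column is only an illustration.

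**The hepatitis parallel.** A reader might take the hepatitis exclusions as a stated principle of removing men to whom an outcome no longer applies. The protocol gives no such rationale and admits men with uncertain history. The closer precedent is the paired vaccination outcomes, and there the restricted version is added, not substituted. That supports keeping the all-men version.

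**It could be left to the analysis plan.** Denominators often are. Here, however, Table 1 is presented as the outcome definitions, and the definition given covers all men. It is a stated choice that can be improved, not an omission.

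**Conclusion.** The point holds as a minor one. Men with a known HIV diagnosis are eligible and count in HIV test uptake, although an HIV screening test does not apply to them. The risk difference shrinks by the factor (1 − *f*): from 10.0 points to between 9.8 and 8.5 for an assumed 2% to 15%, with the lower end of that range more plausible on the Background's evidence. This assumes that known-positive men respond alike in both arms. If they report no test, the risk ratio is unchanged and the power lost is at most a few points, for an outcome on which the protocol makes no power claim.

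The remaining cost is interpretive: the proportion is not cleanly uptake among men who could be linked to HIV testing. The primary outcome, the sample size, Hypotheses 1 and 2 and the other parts of Hypothesis 3 are not affected.

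**What to change.** In Table 1 and under Secondary analyses, define HIV test uptake among men who report no HIV diagnosis in the baseline survey, with that group as denominator in both arms. Keep the all-men version as a supporting analysis, in line with the two versions of HBV vaccination uptake. The group is fixed before randomisation, so the restricted comparison remains randomised. Stating it in advance also avoids a later choice of denominator after the data are seen.

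The cost is one clause in each place and a slightly smaller denominator for this one outcome (for example 315 instead of 350 per arm at an assumed 10%). No new procedure is needed, provided that the baseline item on diagnoses identifies HIV separately from other infections. The baseline questionnaire is not shown, so this should be confirmed.

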**Fig. 1 Fig1:**
[figure not shown]
Trial design to evaluate a crowdsourced intervention to increase hepatitis testing among MSM in China

### Study setting and recruitment

This study will be conducted online. All recruitment, enrolment, intervention delivery, and data collection will occur through mobile phones and social media smartphone apps. Nearly 70% of the adult population in China owns a smartphone, and 95% of all netizens in China access the internet using a mobile phone [27, 28]. In this study, participants will be recruited through an announcement promoted via social media accounts operated by several local MSM organizations. The announcement will include a link connecting men to the online baseline survey to be completed using a smartphone. The link will remain active until 700 eligible men have enrolled.

Once enrolled, WeChat (Tencent Holdings Limited, Shenzhen, China) will be used to deliver messages and collect confirmatory photos of hepatitis test reports from participants. Additionally, men randomly assigned to the intervention arm will view crowdsourced images and videos through WeChat. WeChat is a multipurpose social media smartphone app with messaging and multimedia functionality. The app had approximately 900 million daily active users in 2017, most of whom live in China, and is commonly used to send and share private messages, social media posts, images, and videos [29].

